#### Descriptive variables

2.7.4.

Demographic and medical variables are evaluated to characterize the sample and to assess equivalence across study conditions. Caregivers also report their relationship to the patient and whether they live with the patient. Medical comorbidities are assessed at baseline only; all other medical factors are collected at each timepoint. Patients and caregivers complete a checklist of eight or nine chronic medical conditions, respectively [57]. Patient functional status is also measured with a 1-item self-reported ECOG measure [28]. Patient cancer information is collected via chart review. Patients and caregivers also report their physical and mental healthcare use in five domains (e.g., number of emergency room visits, outpatient visits) in the past 3 months at baseline and over the study period (past 2 months and 3 months at first and second follow-ups, respectively) [57,58]. Additionally, participants report prescribed and over-the-counter medications [59,60].

Finally, measures of symptom severity are administered at all timepoints to characterize the sample. For patients and caregivers, fatigue severity is measured with four FSI items [29,30], and sleep disturbance, cognitive concerns, anxiety, and depressive symptoms are each assessed with a 4-item PROMIS measure [39,48,49,61–63]. For patients, incontinence and diarrhea are assessed with 4-item and 6-item PROMIS measures, respectively [64].

## Statistical analyses

3.

### Preliminary analyses

3.1.

#### Missing data/attrition

3.1.1.

We will examine demographic and medical factors at baseline that might predict dropout using logistic regression. For Aims 1 and 2 described below, all randomized participants will be included in intent-to-treat analyses [65]. Second, for participants who miss assessments, we will use full information maximum likelihood (FIML) to handle missing data without disregarding any incomplete cases.

#### Analyses of potential covariates

3.1.2.

*T*-tests and chi-square analyses will be used to examine differences between study conditions on potential baseline covariates (e.g., demographics, medical factors). Any differences will be considered when interpreting results, and factors that differ between groups will be included as covariates in sensitivity analyses.

### Analysis for aim 1

3.2.

Linear mixed effects modeling (R lme4) [66] will be used to test the hypothesis that ACT will improve the primary outcomes of patient fatigue interference and caregiver burden as compared to education/support. The model for each outcome will include the main effects of time (as categorical) and condition (ACT vs. education/support) and the time-by-condition interaction. Time will be dummy coded using two dummy variables, with baseline as the reference group. A treatment effect will be evidenced by a significant time-by-condition interaction. If the treatment effect is significant, follow-up tests (R emmeans) [67] will be performed to examine group differences at each follow-up.

We estimated the effect size based on the difference between study conditions on the primary outcomes of patient fatigue interference and caregiver burden at 3 months post-intervention. In our pilot RCT in advanced GI cancer, at 3 months we found a medium effect (*d* = −0.60) of condition (ACT vs. education/support) on patient fatigue interference and a small effect (*d* = −0.18) of condition on caregiver burden [21]. In contrast to our pilot, the current trial has a booster session to maintain ACT’s effects. Minimal clinically important differences (MCIDs) or clinically meaningful changes on the Fatigue Interference subscale of the FSI have been reported for cancer populations (range = 0.39–1.63) [68]. MCIDs in caregiver burden have yet to be determined. Estimates of treatment effects from pilots are imprecise [69,70]; thus, we examined results across relevant ACT trials and recommendations regarding MCIDs [71,72] to inform our power calculation. Although ACT has rarely been studied with cancer caregivers, it had a medium effect (*d* = −0.39) on dementia caregivers’ depressive symptoms – which are strongly correlated with caregiver burden [73] – relative to psycho-education at 6 months post-intervention [74]. Additionally, ACT had medium to large effects on mental health outcomes in a meta-analysis of RCTs for clinical populations [75]. In the absence of an established MCID for a self-report measure, a standardized effect size of 0.30–0.50 is recommended to estimate the MCID [71,72]. Thus, we estimate a moderate effect size of *d* = −0.40 for both primary outcomes. With *N* = 170 dyads at 3 months post-intervention (assuming 30 % attrition), we will have 85 % power (α = 0.05, two-tailed) to detect a Cohen’s *d* = −0.40 in a linear mixed model. The estimated attrition is based on our pilot data [21] and survival rates in advanced GI cancer [76].

### Analysis for aim 2

3.3.

Linear mixed effects modeling (R lme4) [66] will be used to test the hypothesis that ACT will improve secondary outcomes as compared to education/support. For outcome measures that only patients or caregivers complete, models will include main effects of time (as categorical) and condition and the time-by-condition interaction. Treatment effects will be evidenced by a significant time-by-condition interaction. For outcomes reported by patients and caregivers, multilevel modeling for dyadic data will be used [77,78]. The model will include the main effects of time, condition, and social role (patient vs. caregiver) as well as all two and three-way interactions. The time x condition x role interaction will estimate the degree to which the treatment effect is different for patients and caregivers. The *p* values from the analyses will be adjusted using the Sidak approach to control for the familywise Type I error rate due to correlated multiple secondary outcomes. If treatment effects are significant, follow-up tests (R emmeans) [67] will be performed to examine group differences at each follow-up.

### Analysis for aim 3

3.4.

Cross-lagged panel models in Mplus [79] will be used to test the hypothesis that increases in psychological flexibility will mediate ACT’s effects on primary outcomes (patient fatigue interference and caregiver burden). Outcomes will be examined in separate models that include condition, the mediator (assessed at baseline and 2 weeks post-intervention), and the outcome at all time points. To evaluate model fit, we will use the comparative fit index (CFI) and the root mean square error of approximation (RMSEA), with CFI ≥0.95 and RMSEA ≤0.05 indicating close fit [80]. The indirect effect of condition on each outcome via psychological flexibility will be quantified using the product of the two relevant effects and tested using bootstrapped confidence intervals (CIs) accounting for nonnormality [81]. A total of 10,000 bootstrapped samples will be drawn, and the indirect effect will be considered statistically significant at *p* < .05 if the 95 % CI does not include zero.

### Analysis for aim 4

3.5.

We will use the same analytic approach, as detailed above for Aim 3, to explore the extent to which changes in mindfulness/acceptance and commitment/behavior change processes mediate the effects of ACT on primary outcomes. Outcomes will be examined in separate models that include condition, both mediators (assessed at baseline and 2 weeks post-intervention), and the outcome at all time points.

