### Randomization and blinding

2.4.

Following baseline assessments, dyads are randomly assigned to ACT or education/support using stratified block randomization to balance the groups by patient age (<65 yrs. vs. ≥65 yrs.) and performance status (patient-reported ECOG scores 0 or 1 vs. 2 [28]). Performance status informs treatment decisions for advanced GI cancer [33]. The statistician uses the R package “blockrand” [34] to generate random assignments within blocks. Randomly varying block sizes of 2 and 4 are used to maintain allocation concealment and ensure balanced allocation to study conditions. Following randomization, study condition assignments are identifiable to participants, interventionists, their supervisors, and staff mailing intervention materials. Other investigators, outcome assessors, and data analysts are blinded.

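### Covariates for the adjusted sensitivity analysis are picked by baseline significance tests between randomized arms, so chance imbalance rather than prognostic value decides what is adjusted for

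*Protocol article*

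**What the plan says.** Section 3.1.2 (Analyses of potential covariates) plans t-tests and "chi-square analyses will be used to examine differences between study conditions on potential baseline covariates (e.g., demographics, medical factors"). It gives the results two uses. The first is informal: "Any differences will be considered when interpreting results". The second is a selection rule: "factors that differ between groups will be included as covariates in sensitivity analyses". No threshold is stated, and the candidate variables are given only by example.

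Section 2.7.4 (Descriptive variables) says that demographic and medical variables are collected "to characterize the sample and to assess equivalence across study conditions".

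Section 2.4 (Randomization and blinding) states that "dyads are randomly assigned to ACT or education/support using stratified block randomization". The stratification factors are patient age (under 65 versus 65 or older) and patient-reported ECOG (0 or 1 versus 2).

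The primary model in section 3.2 is fixed separately: "The model for each outcome will include the main effects of time (as categorical) and condition (ACT vs. education/support) and the time-by-condition interaction". It names no covariates. The two stratification factors are not named in any model that the article describes.

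**The concern.** When allocation is random and concealed, a baseline difference between arms can arise only by chance. A t-test or chi-square test of that difference addresses a null hypothesis already known to be true. Its p-value says nothing about whether a variable needs adjustment, and a non-significant result does not show the equivalence that section 2.7.4 mentions.

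As a selection rule, the test looks only at imbalance. Adjustment is worth making for factors that predict the outcome, and the rule never asks about that. It can pass over a strong predictor with a moderate imbalance and bring in a factor unrelated to either primary outcome.

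Two things are at stake. The only covariate-adjusted check of the primary results that the article describes has a content that depends on the data. And the clause on interpretation sets no rule for how much a chance difference may count, so it could be used to discount a result or to support it.

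**Working it through.** **Inputs from the article.** Stratified block randomization with blocks of 2 and 4 (section 2.4); 244 dyads, hence 122 per arm at equal allocation (section 2.1); 30% attrition by 3 months (section 3.2); baseline treated as one of three response times, with the treatment effect read from the time-by-condition interaction (section 3.2). The article states no figure for the number of baseline tests or their threshold, so there is no figure of its own to reproduce here.

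**1. How often the rule fires by chance.** Assume k independent tests at 5%. The expected number of significant differences is 0.05k, and the probability of at least one is 1 − 0.95^k.

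| k | expected number | P(at least one) |
|---|---|---|
| 5 | 0.25 | 0.23 |
| 10 | 0.50 | 0.40 |
| 20 | 1.00 | 0.64 |
| 30 | 1.50 | 0.79 |

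**2. What it selects.** Under randomization each tested factor is selected with probability 0.05, whether or not it predicts the outcome. In a simulation with 10 independent covariates, 85 per arm and 20,000 trials per scenario, a covariate correlated 0.5 with the outcome was selected in 4.8% to 5.1% of trials, and at least one covariate was selected in about 40%.

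**3. What happens to the stratification factors.** Take the two factors as crossed, giving four strata. An unfinished block of 4 leaves an excess of at most 2 in a stratum. Each level of a factor spans two strata, so its counts differ between arms by at most 2 × 2 = 4. Tested in their stratified form, these factors will hardly ever be selected, although the design treats them as important enough to balance.

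**4. What adjustment does to the planned interaction.** If a covariate enters as a main effect, its contribution is the same at every time and cancels from each person's change from baseline. With complete data the interaction is therefore unchanged. With unit SD and an assumed within-person correlation of 0.5, its standard error is √(4 × 0.5/122) = 0.128, which matches a simulation of the random-intercept model (0.128 with and without the covariate). With 30% random loss at 3 months and a covariate correlated 0.5 with the outcome, the standard error is 0.145 without it and 0.144 with it.

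**5. What adjustment does to the group contrast at a follow-up.** Here the covariate does not cancel. In the same setting with loss, the 3-month contrast has standard error 0.146 unadjusted and 0.129 adjusted, a reduction of 1 − 0.129/0.146 = 12%.

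**The case against.** The strongest reply is about consequence. The rule is confined to sensitivity analyses, the primary model is fixed without covariates, data analysts are blinded, and the selection rule itself is written down in advance. No primary estimate or p-value depends on the baseline tests. All of this stands. A reader might infer that the type I error of the primary test is inflated, or that the primary analysis is itself data-driven. The article does not support either reading.

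A second reply is that the loss of efficiency is overstated. This also stands for the primary effect. In a simple comparison at one follow-up with 85 per arm, a standardized effect of 0.40 and a covariate correlated 0.5 with the outcome, power is 0.739 unadjusted, 0.743 with covariates chosen by baseline tests and 0.852 with the prognostic covariate named in advance. It is tempting to quote this as the power that the trial gives up. It does not carry over, because the planned test is the time-by-condition interaction, which a main-effect covariate hardly changes (step 4).

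A third reply is that 64% rests on an assumed 20 independent tests. This is so. The baseline variables are correlated, two factors are balanced by design, and section 2.7.4 attaches the equivalence purpose only to demographic and medical variables, with symptom measures there to describe the sample. The figure shows how readily the rule fires. It does not measure bias, and a factor unrelated to the outcome would leave the adjusted estimate essentially where it was.

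None of these replies defends the method. Nor is this detail left to an analysis plan that is not shown, because the article states the rule itself.

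**Conclusion.** The concern holds with a limited scope. Section 3.1.2 fixes a poor selection rule: it adjusts for chance imbalance, disregards prognostic value, leaves the adjusted sensitivity model undetermined until the arms are compared, and invites unstructured use of chance differences in interpretation. The equivalence wording in section 2.7.4 asks of these tests something that they cannot show.

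The primary analysis is not affected. Depending on how many variables are tested, the rule would bring in at least one covariate by chance in 23% (5 tests) to 79% (30 tests) of trials like this one, assuming independent tests at 5%. Naming covariates in advance would give a check whose content is known beforehand and somewhat more precise group contrasts at each follow-up (about 12% in standard error at 3 months, if the covariate correlates 0.5 with the outcome). It would not give more power for the primary interaction. The change is worth making because it is sound practice at almost no cost, not because the main result is in danger.

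**What to change.** - Delete the between-arm baseline tests and the clause that lets differences influence interpretation. Report baseline by arm descriptively, without p-values, and remove the equivalence wording from section 2.7.4.
- Before unblinding, fix one adjusted sensitivity model for each primary outcome. Include the stratification factors (patient age group and ECOG) and a short named list of prognostic factors already collected, such as cancer treatment status and baseline depressive symptoms. For caregiver burden, use the caregiver's own depressive symptoms.
- State whether each covariate enters as a main effect or also with time. A main effect can sharpen the group contrasts at follow-up. A covariate-by-time term is needed if a covariate is meant to sharpen the time-by-condition effect, and it helps only where the covariate predicts change.
- Do not add the baseline outcome score as a covariate while baseline is one of the responses in the mixed model. It belongs only in a model where the follow-ups alone are the response.

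The cost is wording in the protocol and analysis plan. Design, sample size, data collection and the primary model stay as they are.

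### Entered as main effects, the imbalanced baseline factors of section 3.1.2 would leave the time-by-condition test almost unchanged, so its sensitivity analysis says little about robustness to imbalance

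*Protocol article*

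**What the plan says.** Section 3.1.2 compares the arms on baseline characteristics with t-tests and chi-square tests. It then says that any differences will be weighed in interpretation and that "factors that differ between groups will be included as covariates in sensitivity analyses". It does not say whether a covariate enters as a main effect only or also by time.

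Section 3.2 fixes the primary model: "The model for each outcome will include the main effects of time (as categorical) and condition (ACT vs. education/support) and the time-by-condition interaction". Baseline is a level of time, not a predictor: "Time will be dummy coded using two dummy variables, with baseline as the reference group". The test is fixed as well: "A treatment effect will be evidenced by a significant time-by-condition interaction". If it is significant, "follow-up tests (R emmeans) [67] will be performed to examine group differences at each follow-up".

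Section 3.3 uses the same structure for Aim 2. For outcomes that only one dyad member reports, "models will include main effects of time (as categorical) and condition and the time-by-condition interaction". For outcomes that both members report, social role and all its interactions are added.

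For missed assessments, section 3.1.1 says "we will use full information maximum likelihood (FIML) to handle missing data without disregarding any incomplete cases". Section 3.2 assumes 30% attrition by 3 months.

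**The concern.** A baseline factor has one value per person. As a main effect it shifts that person's expected score by the same amount at all three visits. The effect tested is a difference in change from baseline, and a constant shift drops out of change.

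An imbalanced factor can distort this effect only if it predicts how scores change over time, and a main effect does not model that part. This is the only sensitivity analysis the article names, and as worded it serves both primary and all secondary outcomes. If programmed literally, its interaction test would nearly copy the primary one. The agreement could then be reported as robustness to imbalance although imbalance in predictors of change had not been adjusted for.

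**Working it through.** **Inputs from the article.** 244 dyads (2.1), taken here as 122 per arm; three assessments; 30% attrition at 3 months (3.2), where 244 × 0.70 = 170.8 agrees with the stated 170; pilot retention of 81% at 2 weeks (Introduction), hence 19% missing; planned d = −0.40 (3.2).

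**Algebra, complete data.** Let μ(a,t) be the mean in arm a at visit t, X a baseline covariate and γ its main effect. Time, condition and their interaction give every arm-by-visit cell its own mean. With a common covariance matrix, the generalised least squares equations give

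μ̂(a,t) = Ȳ(a,t) − γ̂ X̄(a).

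The interaction at visit t is

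[μ̂(ACT,t) − μ̂(ACT,0)] − [μ̂(ES,t) − μ̂(ES,0)],

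with ES for education/support. The term γ̂ X̄(a) appears once with each sign within each arm and cancels. The estimate equals the unadjusted one for any γ̂ and any common covariance matrix.

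**Numerical check.** Random-intercept models were fitted by REML to 300 simulated trials per scenario. The following are assumptions that the article does not supply:
- covariate out of balance by 0.4 SD;
- covariate effect of 0.5 per SD on the outcome at every visit;
- in two scenarios, a further 0.2 per SD at both follow-ups, so that the covariate predicts change;
- true effects of −0.30 at 2 weeks and −0.40 at 3 months;
- random-intercept and residual variances of 0.5 each, so the unit is the outcome SD at a fixed covariate value;
- where there is dropout, 19% missing at 2 weeks and 30% at 3 months.

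Mean 3-month interaction:

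| Scenario | Unadjusted | Main effect | Covariate-by-time |
|---|---|---|---|
| Complete data | −0.393 | −0.393 | −0.391 |
| Complete data, covariate predicts change | −0.323 | −0.323 | −0.403 |
| Dropout unrelated to covariate | −0.400 | −0.400 | −0.402 |
| Dropout depends on covariate | −0.402 | −0.391 | −0.390 |
| Dropout depends on covariate, covariate predicts change | −0.341 | −0.331 | −0.405 |

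The second row can be checked by hand. The expected bias is 0.4 × 0.2 = 0.08, so the unadjusted mean should be about −0.40 + 0.08 = −0.32. The main effect removes none of this; the covariate-by-time terms remove it.

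**How far a main effect moves a single trial.** With complete data the largest change was 1e-14 in the estimate and 2e-9 in the standard error, and significance of the joint interaction test never changed. In the three dropout scenarios, in table order:
- the mean shift was −0.0001, 0.0105 and 0.0107;
- the largest shift was 0.052, 0.061 and 0.091;
- significance changed in 4.3%, 3.3% and 5.0% of trials.

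The standard error changed by at most 0.003. When the covariate predicted change, covariate-by-time terms changed significance in 20% of trials with complete data and 22% with dropout.

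**Group differences at follow-up.** These do respond to a main effect. With complete data and no effect of the covariate on change, the mean 3-month difference moved from −0.197 to −0.396. The expected shift is 0.4 × 0.5 = 0.20.

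**Illustrative size.** Bias in the interaction is the imbalance times the covariate's effect on change. A 0.3 SD imbalance with 122 per arm gives t = 0.3/√(2/122) = 2.34, p about 0.02, so a 5% screening test would select the factor. If it predicts change by 0.3 SD per SD, the bias is 0.3 × 0.3 = 0.09 SD, or 0.09/0.40 = 0.225 of the planned effect. Both inputs are assumptions.

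**The case against.** The strongest reply is that the article never says main effect only. It condenses a fuller plan that is not shown, and the form in which a sensitivity covariate enters could be settled there. This stands in part: covariate-by-time terms are compatible with the wording. But the article names its interactions where it wants them (time-by-condition in 3.2, all role interactions in 3.3), and none is named here. It also fixes the model, the test and the covariate rule; the difficulty lies in how those stated parts combine.

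A reader might go further and infer that this analysis cannot change any result. The documents do not support that. With attrition and full information maximum likelihood, persons with missing visits bring in between-person information, so the interaction can move, in single trials by as much as the 0.09 SD in the example above. The group differences at each follow-up move materially. They are run only after a significant interaction, however, so an all but unadjusted test decides whether the adjusted contrasts are reached.

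It is also fair to say that the size of the bias rests on chosen inputs, that randomization is already stratified by patient age and performance status (2.4), and that 3.1.2 separately weighs imbalances in interpretation. All of this stands. It limits how much is at stake but does not make a main-effect adjustment informative about change.

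**Conclusion.** The point holds in a limited form. If the covariates enter as main effects, the interaction estimate is identical to the unadjusted one with complete data, and on average nearly so under the planned attrition (about 0.00 to 0.01 SD under the assumed dropout patterns). Agreement of the two interaction tests would then be weak evidence of robustness.

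The cancellation is algebra and needs no assumed inputs. The bias left in place does need them: the imbalance and the covariate's effect on change are not in the article, so 0.09 SD is an example and not an estimate for this trial. Nor should the point be read as a fault in the primary analysis. Its model, estimate and error rate are untouched; only a supportive check is weakened, and only when some factor turns out to differ between arms.

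**What to change.** State in section 3.1.2 that each such covariate enters the Aim 1 and Aim 2 sensitivity models with its main effect and its interactions with both follow-up dummies and, in the dyadic models, the matching interactions with role. If the full plan already specifies this, one sentence in 3.1.2 should say so.

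The cost is two extra parameters per covariate beyond the main effect (more in the dyadic models) and no new data. There is a small loss of precision when the covariate does not predict change: with a 0.4 SD imbalance and complete data the mean standard error rose from 0.1277 to 0.1305, about 2%.

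A model of the follow-up scores with baseline score and covariate as predictors should not be offered as interchangeable. It estimates the slope on baseline, whereas the change-from-baseline contrast in effect fixes it at 1. A difference from the primary result could then reflect the new handling of baseline and not the imbalanced factor.

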### Overview of study design

2.1.

This Phase II RCT tests the effects of telephone-based ACT on patient fatigue interference and caregiver burden in advanced GI cancer. We plan to enroll 244 patient-caregiver dyads over about four years. Dyads are randomized to six weekly 50-min telephone sessions of ACT or six weekly 50-min telephone sessions of education/support. Outcomes are assessed at baseline, 2 weeks post-intervention, and 3 months post-intervention (primary endpoint). Dyads in both conditions also complete a 30-min booster phone session one month after the 2-week follow-up. This trial is registered in clinicaltrials.gov (NCT06532877) and approved by the Indiana University Institutional Review Board.

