### Participant eligibility criteria

2.2.

To enroll in this study, both the patient and caregiver need to be eligible and consent to participate. Patient eligibility criteria are as follows: a) unresectable stage III or IV GI cancer according to medical records and the oncologist, b) no significant cognitive impairment as ascertained by medical records and a mental status questionnaire (<3 errors) [27], c) in bed or chair less than half the day (patient-reported Eastern Cooperative Oncology Group [ECOG] score ≤ 2) [28], d) not enrolled in hospice, e) has an eligible, consenting family caregiver, and f) elevated fatigue interference (mean score ≥ 2.5 on the Fatigue Interference subscale of the Fatigue Symptom Inventory [FSI]) [29,30]. In our pilot research in advanced cancer, this level of fatigue interference was significantly associated with clinically meaningful fatigue (score ≥ 3 on the FSI composite measure) [31]. Caregiver eligibility criteria are as follows: a) family or friend caregiver who either lives with the patient or has visited them at least twice a week for the past month, and b) significant caregiving burden (score ≥ 4 on the 4-item Zarit Burden Interview, score ≥ 6 on the 6-item Zarit Burden Interview, or score ≥ 7 on the 7-item Zarit Burden Interview [32]). Clinical cutoffs on the caregiving burden measures have been established in advanced cancer caregivers [32]. Other patient and caregiver eligibility criteria are: a) ≥18 years of age, b) English fluency, c) working phone service, and d) no hearing impairment that precludes study participation.

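### The Aim 1 models are tied to R lme4 with no stated random effects; under an ordinary random-intercept fit, the standard error at the 3-month primary endpoint can be wrong in either direction, most plausibly too small

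*Protocol article*

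**What the plan says.** The article's section 3.2 (Analysis for aim 1) names the tool: "Linear mixed effects modeling (R lme4) [66] will be used to test the hypothesis that ACT will improve the primary outcomes". The fixed effects follow: "The model for each outcome will include the main effects of time (as categorical) and condition (ACT vs. education/support) and the time-by-condition interaction". On coding: "Time will be dummy coded using two dummy variables, with baseline as the reference group". Baseline is thus one of three outcome records per person.

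The decision rule is "A treatment effect will be evidenced by a significant time-by-condition interaction", and then "If the treatment effect is significant, follow-up tests (R emmeans) [67] will be performed to examine group differences at each follow-up".

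Section 2.1 sets the visits and marks the last as primary: "Outcomes are assessed at baseline, 2 weeks post-intervention, and 3 months post-intervention (primary endpoint".

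Section 2.2 requires patients to have "elevated fatigue interference (mean score ≥ 2.5 on the Fatigue Interference subscale of the Fatigue Symptom Inventory [FSI", and caregivers to reach a cut-off on a 4-, 6- or 7-item Zarit form.

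The article does not state the random effects, the within-person covariance, the degrees-of-freedom method or a robust standard error. It gives no SD by visit and no correlation between visits.

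**The concern.** Three visits have six distinct variances and covariances. lme4 adds one residual variance to whatever random effects are specified. A random effect for every visit would use all six, so the residual would be a seventh parameter that cannot be identified. In ordinary use lme4 therefore does not fit an unstructured 3x3 covariance, and its default for this layout is a random intercept: two parameters, with one variance and one correlation for all visits.

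The design gives two reasons to doubt that pattern.

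- **Spread.** Selecting on the outcome construct tends to narrow baseline spread relative to follow-up.
- **Spacing.** Six weekly sessions plus 2 weeks put the first follow-up about 8 weeks after baseline, and six weeks plus 3 months put the second at about 19. The baseline-to-3-month correlation is then likely to be the lowest of the three.

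A random-intercept fit averages over the visits, so its standard error for one particular visit may be wrong. What is at stake is the interval and follow-up test at the primary time point. Likelihood handling of the assumed 30% attrition (sections 3.1.1 and 3.2) also leans on the covariance being right.

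**Working it through.** **The plan's own figure.** The article states 85% power at N = 170 dyads and d = 0.40, two-sided 5%. A plain two-sample comparison gives Φ(0.40/√(2/85) − 1.96) = Φ(2.608 − 1.960) = 74.1%. With baseline adjustment at r = 0.50 the SD becomes √(1 − 0.25) = 0.866, and power is 85.3%. A change score reaches 84.9% at r = 0.62. The 85% is attainable in a mixed model, but the correlation behind it is not given. It can be neither confirmed nor called wrong, and it supplies no covariance for the check below.

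**Inputs.** From the article: 244 dyads, taken as 122 per arm from the balanced blocks (section 2.4); 30% missing at 3 months (section 3.2); 19% missing at 2 weeks, from pilot retention of 81% (Introduction). Assumed: all SDs and correlations, and monotone dropout completely at random (70% with all visits, 11% with baseline and 2 weeks, 19% with baseline only). Correlations are listed as baseline–2 weeks / baseline–3 months / 2 weeks–3 months.

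**By hand, complete data.** A random-intercept fit gives every pairwise change the mean of the three change variances, and every visit the mean of the three visit variances. The actual size of a nominal 5% test is 2Φ(−1.96 × model SE / true SE).

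- *Change contrast* (the baseline-to-3-month interaction coefficient), equal SDs of 1, correlations .65/.50/.65. The change variances 2(1 − r) are 0.70, 1.00 and 0.70, with mean 0.80. The SE ratio is √(0.80/1.00) = 0.894, so the size is 2Φ(−1.753) = 8.0%.
- *3-month group difference*, SDs .8/1.05/1.15. The mean variance is (0.640 + 1.1025 + 1.3225)/3 = 1.022. The ratio is √1.022/1.15 = 0.879, so the size is 8.5%.
- *3-month group difference*, falling SDs 1/.95/.85. The mean variance is (1 + 0.9025 + 0.7225)/3 = 0.875. The ratio is √0.875/0.85 = 1.10, so the size is 3.1%.

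**With dropout, large sample.** The model variance is A⁻¹ and the true variance is A⁻¹BA⁻¹. Here A = Σ n·Z′V⁻¹Z and B = Σ n·Z′V⁻¹ΣV⁻¹Z, summed over dropout patterns, with V the fitted and Σ the assumed true covariance.

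| Assumed SDs; correlations | Change contrast: SE ratio (size) | 3-month difference: SE ratio (size) |
|---|---|---|
| (a) equal; .6/.4/.6 | 0.89 (8.2%) | 0.98 (5.4%) |
| (b) .8/1.05/1.15; .5/.4/.6 | 0.89 (8.1%) | 0.85 (9.5%) |
| (c) .8/1/1; all .5 | 1.00 (5.0%) | 0.92 (7.1%) |
| (d) 1/.95/.85; all .5 | 1.03 (4.3%) | 1.11 (2.9%) |
| (e) 1/1.2/1; all .5 | 1.08 (3.5%) | 1.07 (3.6%) |
| (f) equal; .4/.55/.45 | 1.08 (3.4%) | 1.01 (4.7%) |

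Patterns (a) to (c) follow the features of the design. Patterns (d) to (f) need spread that falls, spread that peaks at 2 weeks, or the longest gap to be the best correlated. With the true unstructured covariance, each size is 5.0%.

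**The joint test.** The size of the 2-df interaction test over the patterns tried is 4.7% to 6.1%.

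**After the gate.** Suppose an effect of 0.4 at 2 weeks has vanished by 3 months. The article adds a booster session to maintain effects, so fading is a case it foresees. A false 3-month group difference after a significant interaction then occurs in 6.5% of trials under (c) and 9.0% under (b). In the same scenario under (a), the interaction test has about 90% power with a random intercept and about 95% with an unstructured covariance.

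**The case against.** The strongest reply is that the article never says random intercept only. The random-effects structure is a detail that an article commonly leaves to the full protocol or SAP, and naming lme4 does not settle it. A random intercept plus a random linear slope is routine in lme4, uses four parameters and is identifiable with three visits. With that fit and the dropout above, the change contrast under correlations .65/.50/.65 goes from 7.8% to 5.0%. Under (b) it goes from 8.1% to 5.0%, and the 3-month difference from 9.5% to 4.4%. This stands, and it makes the concern conditional. What remains is that the article does fix the tool, and in ordinary use the tool cannot fit the covariance that is safe whichever way the data fall.

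The second reply is that the decision rests on the interaction. Read as a joint test, it is nearly unaffected, and under a global null the gate caps false 3-month claims at its own rate of at most 6.1%. This also stands. It does not repair the 3-month interval, and it does not protect the follow-up test once a real early effect has opened the gate. Nor does the article say that the two interaction coefficients are tested jointly.

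A reader might infer that the 3-month standard error will be too small and that false positives exceed 5% for both primary outcomes. The documents do not support that. They give no SDs or correlations, and patterns (d) to (f) show standard errors that are about right or too large. For caregivers, selection is on shorter Zarit forms while the outcome is the 12-item form, so any narrowing of baseline spread is indirect and is not quantified here.

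**Conclusion.** The point holds in conditional form. If the Aim 1 models are fitted in lme4 with a random intercept alone, the standard error and interval at the 3-month primary endpoint can be wrong in either direction. The SE ratio runs from about 0.85 to 1.12, and nominal 5% tests of the 3-month contrasts run at about 3% to 9.5%. Too small is the more plausible direction, because the screening and the visit spacing both point that way. The primary interaction test, if joint, is only slightly affected.

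The consequence is therefore confined to the 3-month estimate's interval, the follow-up tests after the gate, and a possible loss of power that was shown for one pattern only. All of this rests on assumed SDs and correlations and on dropout completely at random. The point deserves correction before analysis, but it is not a demonstrated error in the trial's main test.

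**What to change.** Fit the Aim 1 models, and the patient-only sleep interference model in section 3.3, with an unstructured 3x3 covariance across visits. R mmrm does this, as does nlme gls with visit-specific variances and a general correlation. Use Satterthwaite or Kenward-Roger degrees of freedom where the software supports them. Keep the fixed effects as planned.

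The cost is a change of R function, one sentence in the analysis plan, and four extra covariance parameters (six instead of two), with negligible loss of precision at 244 dyads.

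If lme4 is kept, state the random effects and add at least a random slope in time to the random intercept. That removes most of the inflation in the patterns checked, but it remains a restricted covariance.
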